For continuous biomechanical outcome data measurements, we plan to sub-sample six players per team. Given 20 teams per study arm, this will give us 80% power to detect effects of size (*a*) 0.44 or (*b*) 0.63 standard deviations (SDs) between study arms assuming a clustering effect described by an intracluster correlation coefficient of (*a*) 0.1 or (*b*) 0.4. The SDs refer to total player-to-player variability in the biomechanical outcome, and the intracluster correlation coefficient is the ratio of between-team variability to total variability. To achieve six players with complete biomechanics data, we will enlist eight, expecting ∼20% dropout based on our previous training study. These sample size calculations also provide a conservative lower bound for power for the analysis of attitude scores, as they were based on six players per team, and the change in attitude scores will be available for closer to 18 players. The study will therefore have >80% power for detecting changes in neuromuscular, biomechanical and attitude parameters as described by an effect size of 0.44 SDs.

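### The closing claim of more than 80% power at 0.44 SD omits the ICC condition that the same paragraph attaches to it; at the article's own ICC of 0.4, power is about 50%

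*Protocol article*

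**What the plan says.** The second paragraph of the Sample size section deals with continuous outcomes. For the biomechanical measures, "we plan to sub-sample six players per team", and eight are enlisted per team to allow for dropout. The paragraph continues: "Given 20 teams per study arm, this will give us 80% power to detect effects of size" 0.44 SD in case (a), or "0.63 standard deviations (SDs) between study arms assuming a clustering effect described by an intracluster correlation coefficient of" 0.1 in case (a) and 0.4 in case (b). So 0.44 SD belongs to ICC 0.1 and 0.63 SD to ICC 0.4. The units are defined: "The SDs refer to total player-to-player variability in the biomechanical outcome", and "the intracluster correlation coefficient is the ratio of between-team variability to total variability".

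The paragraph then turns to attitudes: "These sample size calculations also provide a conservative lower bound for power for the analysis of attitude scores". The reason given is that the calculation used six players per team, while attitude change will be available for nearly 18. It concludes that the "study will therefore have >80% power for detecting changes in neuromuscular, biomechanical and attitude parameters as described by an effect size of 0.44 SDs".

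Two other places bear on this. The first paragraph of Sample size puts 10 of each arm's 20 teams in Ballarat and 10 in Perth. The section on biomechanical, neuromuscular and mobility outcome measures gives the full test battery to Perth teams only. Ballarat teams receive a field subset: knee movement and position sense, isometric strength, standing balance and the agility cone test.

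**The concern.** The conclusion does not follow from the two scenarios it is drawn from. It keeps the effect size of the favourable ICC, drops the condition, and extends the result to three families of outcome. The only added argument, the larger number of respondents, concerns attitude scores and does nothing for neuromuscular or biomechanical measures.

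The article makes changes in kinematics, knee loading, muscle co-contraction and neuromuscular measures explicit hypotheses. A reader who relies on the closing sentence would take a null result on any of these as good evidence against a difference of 0.44 SD. Under the less favourable ICC that the authors themselves allow for, the trial would miss such a difference about half the time.

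**Working it through.** **Inputs.** From Sample size: k = 20 teams per arm; m = 6 players per team (about 18 for attitude scores); ICC = 0.1 or 0.4; SD set to 1. For Perth-only outcomes, k = 10 per arm, from the stated split by state. Two-sided alpha of 0.05 is an assumption. It is supported by the reproduction below: one-sided 0.05 would give 0.39 and 0.56 SD, which do not match the article.

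**Formulas.**
- Design effect DE = 1 + (m − 1) × ICC
- Effective number per arm n = k × m / DE
- Effect detectable with 80% power = (1.960 + 0.842) × √(2/n)
- Power at 0.44 SD = Φ(0.44/√(2/n) − 1.960)

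**Reproducing the article's figures (k = 20, m = 6).**
- ICC 0.1: DE = 1.5, n = 120/1.5 = 80, detectable effect = 2.802 × √(2/80) = 0.443 SD (article: 0.44).
- ICC 0.4: DE = 3.0, n = 120/3.0 = 40, detectable effect = 2.802 × √(2/40) = 0.627 SD (article: 0.63).

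**Power at 0.44 SD and detectable effects.**

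| Outcomes | k | m | ICC | DE | n | Effect at 80% power | Power at 0.44 SD |
|---|---|---|---|---|---|---|---|
| Tests in both states | 20 | 6 | 0.1 | 1.5 | 80 | 0.443 | 79.5% |
| Tests in both states | 20 | 6 | 0.4 | 3.0 | 40 | 0.627 | 50.3% |
| Attitude scores | 20 | 18 | 0.1 | 2.7 | 133.3 | 0.343 | 94.9% |
| Attitude scores | 20 | 18 | 0.4 | 7.8 | 46.2 | 0.583 | 56.1% |
| Perth-only laboratory | 10 | 6 | 0.1 | 1.5 | 40 | 0.627 | 50.3% |
| Perth-only laboratory | 10 | 6 | 0.4 | 3.0 | 20 | 0.886 | 28.5% |

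For example, at k = 20, m = 6, ICC 0.4: 0.44/√(2/40) = 1.968, and Φ(1.968 − 1.960) = 50.3%.

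**Largest ICC at which 0.44 SD keeps 80% power (k = 20).** The effective number required is 2 × (2.802/0.44)² = 81.1 per arm.
- With 18 players: DE may be at most 360/81.1 = 4.44, so ICC ≤ 3.44/17 = 0.20.
- With six players: DE may be at most 120/81.1 = 1.48, so ICC ≤ 0.48/5 = 0.096.

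**Sensitivity.** A t-based calculation on team-level degrees of freedom gives slightly lower power: 48.3% (m = 6) and 54.0% (m = 18) at ICC 0.4 with 20 teams per arm. If all eight enlisted players per team completed testing, power at ICC 0.4 would still be only about 52%.

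**The case against.** The strongest reply is that nothing is hidden. Both scenarios, with correct detectable effects, stand a few sentences above the conclusion. These outcomes do not set the number of teams, which comes from the injury-rate calculation, and no design feature or analysis depends on the sentence. That is all true and limits the weight of the point. It does not make the sentence correct: it states a power that the figures beside it contradict.

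Four stronger readings are tempting, and the documents do not support them.

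- *A reader might infer that calling the calculation a lower bound for attitude scores is wrong.* It is not. The phrase refers to the six-player calculation, and at equal ICC 18 players always give more power: 94.9% against 79.5% at ICC 0.1, and 56.1% against 50.3% at ICC 0.4. It lacks only the equal-ICC condition.
- *A reader might infer that the attitude claim is false.* The article gives no ICC for attitude scores. The claim holds up to about 0.20 and fails above it, so it is unproven rather than refuted.
- *A reader might infer that the SD is too small because changes are analysed.* The article does not say that the SD refers to a single time point. If it did, the change-score SD would be √(2(1 − ρ)) times as large, where ρ is the pre/post correlation: 1.18 at ρ = 0.3, 1.00 at 0.5 and 0.77 at 0.7. The article gives no ρ, so even the direction is unknown.
- *A reader might make much of 79.5% against a claim of more than 80%.* That gap comes from printing 0.443 as 0.44. It justifies writing about 80% for the six-player outcomes, nothing more.

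**Conclusion.** The point holds for the missing condition. With 20 teams per arm, power at 0.44 SD for outcomes on six players per team is about 80% at ICC 0.1 and about 50% at ICC 0.4. For attitude scores on about 18 players it is about 95% and 56%, with 80% reached only up to an ICC of about 0.20.

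For laboratory outcomes taken only in Perth, the basis of 20 teams per arm conflicts with the outcome-measures section. With 10 teams per arm, power at 0.44 SD is about 50% at ICC 0.1 and 28% at ICC 0.4, so the sentence fails for these even under the favourable ICC.

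These figures assume two-sided alpha 0.05, equal team sizes, 10 Perth teams per arm, and the article's own ICC values. The article does not say which ICC is more likely, so 50% is the power under one of its scenarios and not an estimate of the power the trial will have. The result says nothing about power for knee injury rates. The sentence should be corrected, but it is not a flaw in the design.

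**What to change.** Replace the closing sentence with effects detectable at about 80% power, conditional on the ICC and with alpha stated:

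| Outcomes | Basis | ICC 0.1 | ICC 0.4 |
|---|---|---|---|
| Neuromuscular and mobility tests done in both states | 20 teams per arm, 6 per team | 0.44 SD | 0.63 SD |
| Laboratory outcomes measured in Perth only | 10 teams per arm, 6 per team | about 0.63 SD | about 0.89 SD |
| Attitude scores | 20 teams per arm, about 18 per team | about 0.34 SD | about 0.58 SD |

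Keep the statement that the six-player calculation is a conservative lower bound for attitude scores, and add that this holds at the same ICC.

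The cost is wording only. Team numbers, player numbers and analyses stay as they are. The price is that the stated power becomes conditional and less favourable, most of all for the laboratory outcomes.

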### Primary data collectors

All field work procedures are rigidly standardised and based on methods previously developed, piloted and used in similar Australian football studies.^11^ ^35^ ^36^ ^38^ ^41^ The good to high reliability and validity of these data collection methods has already been demonstrated.^36^ ^38^ The day-to-day conduct of the RCT is being coordinated by a project manager in each state.

The appointed project managers train and coordinate the activities of a nominated person within each team (ie, the primary data collector or PDC), who is responsible for data collection on site. The PDC is also the team’s exercise trainer for training sessions and game, which has been a major incentive to attract teams into the study and ensure compliance. It is their role to ensure that the RCT training intervention is run in cooperation with the team coaches, and to ensure that players are compliant and progress to more advanced training tasks as they become more proficient.

It was compulsory for all PDCs to attend a separate formal training session for the intervention arm that covers all study procedures. A detailed procedures manual was disseminated to all PDCs and the clubs they are associated with; these contain the standardised data collection forms for recording exposure, compliance and injuries as well as full details of the coding and classification schemes. During the training sessions, practice exercises on specific examples were undertaken to address any discrepancies before the data collection period starts.

Previous research has demonstrated the use of PDCs in this context as a valid and reliable means of exposure, compliance and injury data collection.^36^ ^38^ ^41^ Club-based PDCs have the particular advantage of knowing all members of the team well and being able to determine very quickly and accurately if a player is missing from a game or training session and determining the reasons why (eg, related to injury?). The accuracy of the PDC activities is being assessed through double counting of exposure and injury data at randomly selected games.^38^ The work being undertaken by the PDCs is not very different from standard practice in Australian Football clubs, which already typically involves the recording of the team members present and any injuries that occur.

### Injury and exposure details

The PDCs record the occurrence of all injuries and their circumstances, and provide injured player details for each game and training session using previously used standardised methods.^12^ ^35^ ^41^ A standardised form is used to provide a simple description of injury and notification that the player was seen by a doctor or sent to hospital. This information is obtained from the PDCs each week.

A self-report injury diagnosis will be obtained from the player after they have sought medical or other treatment for that injury. The injured player will also be asked to provide the details of the person who provided their treatment, so that their self-report information can be validated and full details of the diagnosis obtained from their medical practitioner. Medical records pertaining to injuries sustained during the games will also be obtained, and the injury descriptions reviewed by an associate investigator with medical qualifications. A medical diagnosis will be obtained and coded for each case, and this will be checked with the original notification of injury.

For each player, the amount of time spent playing Australian Football (both competition and training) over each week of the trial is recorded by the PDC. This is done in accordance with the methods previously developed for other community-based Australian Football injury studies.^12^ ^35^ ^41^ ^43^ Exposure is recorded during each training session and game.

### Biomechanical, neuromuscular and mobility outcome measures

The neuromuscular and biomechanical changes induced by the various aspects of the training programmes have already been demonstrated in elite footballers. It is, however, important to assess the effectiveness of the training programme on adaptations and injury rates in community-based footballers. Theoretically, these changes should reduce ligament loading and the risk of injury. However, before they can be readily implemented, it is essential to see if these changes are indeed associated with reduced injury rates. This combination of results will provide confidence in the theoretical basis for the laboratory-based studies used to investigate injury mechanisms and reduction.

To this end, biomechanical measures related to reduction in knee ligament loading will be collected from a subset of players as mentioned above. These measures will be taken while the players perform cutting and landing tasks and entail: (*a*) knee flexion angle at heel strike; (*b*) frontal plane kinematics (position and movement) trunk and pelvis position relative to foot; and (*c*) hamstrings and quadriceps muscle activation patterns. Neuromuscular measures to be taken are: (*a*) knee movement sense and position sense; (*b*) time to generate maximum knee extension and flexion torque in response to a light stimulus; (*c*) isometric knee extension and flexion strength; and (*d*) standing balance. Finally, mobility in the game situation will be assessed by (*a*) agility cone test and (*b*) reaction time to perform the cutting manoeuvres in response to a light stimulus. This battery of tests will be performed on eight players randomly selected from each team in the RCT arms in Perth only and will be taken before training starts and half way into the season. All tests will be performed in the Sports Motion Analysis Laboratory in the School of Sport Science, Exercise and Health at UWA. The cutting and landing tasks will be collected using a 12-camera Vicon 612 system with two force plates to measure kinetic data and a 16-channel telemetry electromyographic system to measure muscle activation patterns. Each participant will perform a series of trials for each task as per the procedures already developed.^14^ ^15^ ^18^ ^19^ Mathematical optimisation algorithms with a cluster marker set have already been developed to improve the repeatability of biomechanical data,^14^ ^15^ ^53^ in some cases by as much as much as 100%.^53^ The neuromuscular parameters assessed in this study will be acquired and processed using established procedures^14^ ^18^ ^32^ ^33^ that are currently used in this laboratory.

In Ballarat, we intend to use some of the neuromuscular and mobility tests selected from the battery of tests performed in Perth. These selected tests will be those that can easily be performed in the field situation. These will be: (*a*) knee movement sense and position sense; (*b*) isometric knee extension and flexion strength; (*c*) standing balance; (*d*) agility cone test. These will also be performed on eight randomly chosen people from each team and taken before training starts and about half way into the season.

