### Sample size

The intervention is being implemented during training sessions and its effects measured during games. A team consists of 18 members and a game lasts ∼100 min (four quarters of ∼20 min plus ∼5 min time added on). Over a 6-month playing season, each team has ∼20 games and so each team will contribute ∼600 game-hours of exposure to knee injury risk. We used a standard cluster randomised trial sample size calculation for comparing rates between a control arm and an intervention arm.^52^ The knee injury rate in the control arm was estimated as 20 per 1000 game-hours. This figure is based on the observation of 60.2 injuries (of all kinds) per 1000 game-hours (from data from Finch *et al*^11^) and an assumption that approximately one-third of Australian Football injuries involve the knee. To have 80% power to detect a reduction in the injury rate of 35% (ie a rate ratio of 0.65) in the intervention arm compared with controls, we would require 8.8 teams in each arm. This calculation does not take account of any clustering effects of injuries by team. From the same data,^11^ we estimate that the coefficient of variation of team injury rates will be 0.35 (ie, standard deviation of team injury rates divided by mean of team rates). Assuming that the clustering effect will be identical in the intervention arm, the number of teams required must be multiplied by 2.27, ie, 8.8×2.27 = 20 teams per study arm over the 2 years. Thus 20 teams (10 in Ballarat, 10 in Perth) will be randomly allocated to each arm of the study across the two playing seasons.

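### Power for the laboratory outcomes is calculated on 20 teams per arm, but these outcomes are measured in Perth only, where each arm has 10 teams

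*Protocol article*

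**What the plan says.** The Sample size section of the protocol article sets the number of teams from the injury rate and fixes the split by state: "Thus 20 teams (10 in Ballarat, 10 in Perth) will be randomly allocated to each arm of the study".

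It then turns to the laboratory sub-sample: "For continuous biomechanical outcome data measurements, we plan to sub-sample six players per team". The power claim follows: "Given 20 teams per study arm, this will give us 80% power to detect effects of size" 0.44 or 0.63 SD, "assuming a clustering effect described by an intracluster correlation coefficient of (*a*) 0.1 or (*b*) 0.4" respectively. The scale is defined: "The SDs refer to total player-to-player variability in the biomechanical outcome". The section closes by claiming power above 80% at 0.44 SD for neuromuscular, biomechanical and attitude parameters together, with no ICC attached.

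The section on biomechanical, neuromuscular and mobility outcome measures describes the full battery and refers back to the same sub-sample of players. It then limits where the battery is run: "This battery of tests will be performed on eight players randomly selected from each team in the RCT arms in Perth only". Ballarat receives four field tests: knee movement and position sense, isometric knee strength, standing balance, and the agility cone test. None of these is a cutting or landing measure.

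**The concern.** The outcomes that the power calculation names, the biomechanical ones, are never measured in 20 teams per arm. Every cutting or landing measure comes from Perth alone, as do the time to generate maximum knee torque (classed as neuromuscular) and the reaction time for cutting manoeuvres (classed as mobility). The calculation's team count is therefore twice what the measurement plan supplies for these outcomes.

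The Research aims and hypotheses section includes hypotheses on kinematics, knee joint loading and co-contraction during cutting and landing, and the Objective asks whether the biomechanical adaptations are associated with lower injury risk. A reader who relies on the stated power could take a null laboratory result as evidence against a 0.44 SD adaptation, when the chance of detecting one was about one in two at ICC 0.1.

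**Working it through.** **Inputs**
- Teams per arm, k: 20 in the power statement; 10 in Perth (Sample size).
- Players per team with complete data, m: 6 (Sample size).
- Effects and ICCs: 0.44 SD with ICC 0.1; 0.63 SD with ICC 0.4 (Sample size). Total SD = 1.
- Significance level: not stated. Two-sided 5% is assumed and tested in step 1.

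**Formulas**
- Design effect: DE = 1 + (m − 1) × ICC = 1 + 5 × ICC, giving 1.5 (ICC 0.1) or 3.0 (ICC 0.4).
- Effective players per arm: n = k × 6 / DE.
- Effect detectable with 80% power: (1.96 + 0.84) × √(2/n).
- Power at effect d: Φ(d / √(2/n) − 1.96).

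**Step 1: reproduce the stated figures (20 teams per arm)**
- ICC 0.1: n = 120/1.5 = 80; detectable effect 2.80 × √(2/80) = 0.443 SD; power at 0.44 SD = 79.5%.
- ICC 0.4: n = 120/3 = 40; detectable effect 2.80 × √(2/40) = 0.626 SD; power at 0.63 SD = 80.4%.

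Both match the protocol's 0.44 and 0.63 SD. A one-sided 5% level would give 0.39 and 0.56 SD, so two-sided 5% with 20 teams per arm is evidently what was used. The arithmetic is sound; the team count is the problem.

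**Step 2: Perth-only outcomes (10 teams per arm)**
- ICC 0.1: n = 60/1.5 = 40; detectable effect 2.80 × √(2/40) = 0.63 SD; power at 0.44 SD = Φ(1.968 − 1.96) = 50.3%.
- ICC 0.4: n = 60/3 = 20; detectable effect 2.80 × √(2/20) = 0.89 SD; power at 0.63 SD = Φ(1.992 − 1.96) = 51.3%.

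| ICC | Effect | Power, 20 teams per arm | Power, 10 teams per arm | Effect detectable with 80% power, 10 teams per arm |
|---|---|---|---|---|
| 0.1 | 0.44 SD | 79.5% | 50.3% | 0.63 SD |
| 0.4 | 0.63 SD | 80.4% | 51.3% | 0.89 SD |

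With a t reference on 2 × (10 − 1) = 18 degrees of freedom, the two power figures at 10 teams per arm are 46% and 47%.

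**Step 3: the closing sentence (0.44 SD, no ICC given)**
- ICC 0.4, 20 teams per arm: n = 40; power = Φ(0.44/√(2/40) − 1.96) = 50.3%.
- ICC 0.4, 10 teams per arm: n = 20; power = Φ(0.44/√(2/20) − 1.96) = 28.5%.
- Attitude scores at 18 players per team, 20 teams per arm: 95% at ICC 0.1 but 56% at ICC 0.4.

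The 0.44 SD claim therefore depends on ICC 0.1 even for outcomes measured in every team.

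**The case against.** **Eight players per team are enlisted.** The protocol says: "To achieve six players with complete biomechanics data, we will enlist eight, expecting ∼20% dropout based on our previous training study". If all eight had complete data, power with 10 teams per arm would be 57% at 0.44 SD (ICC 0.1) and 53% at 0.63 SD (ICC 0.4). That is still far below 80%, and the protocol itself plans on six.

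**Baseline adjustment could recover power.** The hypotheses concern pre-to-post change, and a baseline and a mid-season measurement are both taken. This is a fair qualification of the exact percentages. However, the stated power does not use baseline adjustment and no pre-post correlation is given. Offsetting a halving of teams needs 1 − r² = 0.5, so r of about 0.7, if adjustment shrinks between-team and within-team variance alike.

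**The trial is sized on injury rate.** This is true: the sub-sample is mechanistic, and the injury sample size is untouched. It limits the reach of the point but does not make the stated laboratory power correct.

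**Could the team count be read another way?** The 20 teams per arm are spread across two playing seasons, but counting team-seasons does not raise the Perth share above 10 per arm.

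**A stronger reading is tempting.** A reader might infer that the Perth restriction cuts power from 80% to 28% at ICC 0.4. The documents do not support that. They pair ICC 0.4 with 0.63 SD, and at 0.44 SD with ICC 0.4 power was only about 50% before any restriction. The like-for-like fall at ICC 0.4 is from 80% to 51%. The 28% figure combines two faults: the halved team count and the ICC missing from the closing sentence.

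**Conclusion.** The point stands as an internal inconsistency, not as a calculation error. For all Perth-only measures the stated 80% power is not what the design provides. Like for like, it is about 50% at 0.44 SD (ICC 0.1) and about 51% at 0.63 SD (ICC 0.4), and the effects detectable with 80% power are 0.63 and 0.89 SD. Separately, the closing claim at 0.44 SD lacks its ICC condition. At ICC 0.4 with six players per team, power there is about 50% with 20 teams per arm and 28% with 10.

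These figures rest on a two-sided 5% level (assumed, and supported by the reproduction), six complete players per team, and the protocol's own unadjusted comparison on the total SD. They do not extend to the four field tests run in both states, which keep 20 teams per arm, to the team count behind the attitude scores, or to the injury outcome.

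**What to change.** Restate the power in the Sample size section by outcome set:
- **Perth-only measures** (all cutting and landing kinematics, kinetics and muscle activation, time to maximum torque, cutting reaction time): 10 teams per arm, with 80% power at 0.63 SD (ICC 0.1) or 0.89 SD (ICC 0.4).
- **The four field tests done in both states**: 20 teams per arm, with 0.44 SD (ICC 0.1) or 0.63 SD (ICC 0.4) as now.
- **Attitude scores**: keep the statement on all teams.

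Limit the closing sentence to outcomes measured in both states and attach ICC 0.1 to its 0.44 SD. Deleting only the word biomechanical would not be enough: time to maximum torque would stay covered as a neuromuscular measure, and the ICC condition would still be missing. State the significance level alongside.

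The cost is a change of wording and a less favourable stated figure. No extra players or tests are needed.
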